#### *6.5 Randomization Procedures*

We will identify 30 similarly sized communities in Shinyanga District Council. For potential inclusion, communities must have an active cadre of CHWs, have similar numbers of households and schools, be noncontiguous or separated by natural boundaries, and be within 5 km of a RCH facility that is providing Option B+. The impact evaluation team will assign communities to the intervention or comparison group using simple randomization (using the sample command in STATA), consistent with previous studies.

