Increasing retention in the PMTCT cascade is particularly critical in high-burden, priority countries like Tanzania, where 6.2% of women aged 15-49 are HIV-positive and nearly one quarter of pregnant women living with HIV do not receive ARVs/ART for PMTCT. Notably, in Tanzania, achievements in PMTCT could have important impacts on the national epidemic, as 1 out of every 5 new HIV infections are due to mother-to-child transmission – an estimated 36,225 infections per year. In September 2013, Tanzania began rolling out 'Option B+' to all 6,270 reproductive and child health (RCH) facilities, the PMTCT strategy whereby HIV-infected pregnant women receive ART throughout their lives regardless of clinical stage. By simplifying service delivery, drug regimen, and reducing the number of steps that mothers need to negotiate (such as CD4 testing), Option B+ is expected to improve retention in the PMTCT cascade. However, the postulated benefits of Option B+ are predicated on mothers remaining on lifelong ART, starting at the time of HIV diagnosis. Thus, a critical unresolved issue is whether *asymptomatic* women who learn their HIV status during pregnancy will initiate and adhere to ART under Option B+.

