#### **4. STUDY SETTING AND RATIONALE**

Our study will be conducted in Shinyanga, one of Tanzania's 30 regions in the northern "Lake Zone" where HIV prevalence is 7.4% (8.1% among women). Under Tanzania's Reproductive Child Health Platform Approach and Option B+, ANC, postnatal care, and HIV treatment and care are now provided in the majority of Tanzania's 6,270 reproductive and child health (RCH) clinics. There are approximately 12,000 CHWs in Tanzania, including 1,512 CHWs in Shinyanga Region who serve 490 villages. Under the current structure, however, CHWs in Shinyanga do not participate in any activities related to the provision of HIV care for HIV-infected pregnant women, PMTCT, or Option B+.

The current study would connect these two separate programs and subsequently evaluate the effectiveness of providing Option B+ through CHW care. While previous studies have found CHWs to be effective, they have a clear focus on preventing infant infections and improving infant health; none evaluated whether the mother was retained in care after her baby was delivered and whether she was adherent to ART. Furthermore, none have been conducted since the implementation of Option B+, which is a new and integrative approach to PMTCT with specific challenges for health care delivery.

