## **7. METHODOLOGY**

### *7.1 Definition of Baseline and Endline Cohorts of HIV-Infected Pregnant Women*

We will retrospectively abstract data from routinely collected information in CHW logs and facility registries of patient medical information (see **Figure 1** for an overview of the impact and process outcomes). The research team will collect data from two 6-month cohorts (baseline and endline) of women who are 90 days postpartum to ensure that we can measure retention in care and adherence at 90 days postpartum (**Figure 4**):

- The baseline cohort will include HIV-infected women who were 90 days postpartum between July 1 and December 31, 2014; this corresponds to infants born between April 1 and September 30, 2014. These women are unexposed to the intervention.
- The endline cohort will include HIV-infected women who are 90 days postpartum between May 1 and October 31, 2015, corresponding to infants born between February 1 and July 31, 2015. These women will have been exposed to the intervention during the last 4-9 months of their pregnancy and during their entire 0-90 day postpartum period. This is a reasonable amount of exposure to the intervention given that, on average, women in Tanzania are 5.4 months pregnant at their first ANC visit when they have the initial opportunity to initiate ART.

**FIGURE 4.** Cohorts for Baseline and Endline Data Collection

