All three indicators will be measured primarily from ANC records, though we will also back check these records with CHW logs to ensure accuracy and quality of the data. We will analyze all three measures through difference in difference strategy in order to capture differences in outcome between the control and treatment groups.

**7.5. Evaluation Question #2:** Is the impact of integrating community-based MNCH and PMTCT

*services on retention in care and adherence greater among women who had more contact with CHWs?*

To answer this question, we will monitor the CHW logs to measure (a) the duration of visits with CHWs and (b) the frequency of visits (per week, per month). We will then compare the frequency and duration of visits to each woman's retention in the program, and their level of participation (measured through adherence to ART) to find the correlation between CHW contact and participation.

*7.6. Evaluation Question #3: Is integration of community-based MNCH and PMTCT services acceptable and feasible for CHW, health facility staff, and pregnant and postpartum women, and are there potential spillover benefits on other maternal health outcomes?*

We will conduct a mixed methods process evaluation, including quantitative analysis of process outcomes feedback from stakeholders (two facility personnel, five CHWs, five clients, two Amref staff), and in-depth interviews with women, in order to better understand the effectiveness and feasibility of the intervention. We will focus our efforts on answering the following key questions:

- a. Was the intervention implemented as intended? Was there heterogeneity in implementation? Were standard operating protocols followed consistently and correctly?
- b. Were there community- or facility-level factors that influenced the success of the intervention? Was the intervention impeded by the time availability of CHW or facility staff?
- c. Did the intervention motivate pregnant and postpartum women? How? What aspects were motivating and why? Did the intervention inadvertently increase stigma?
- d. What were successful or challenging aspects of the intervention throughout the causal chain (**Figure 1**)? What could be improved?

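### The Option B+ eligibility rule in section 6.5 does not reach back to the baseline pregnancies, so late-starting facilities can add avoidable noise and chance imbalance to the difference-in-differences

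*Protocol*

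**What the plan says.** Protocol section 6.5 lists the conditions for a community to be eligible. On HIV care it asks only that the community "be within 5 km of a RCH facility that is providing Option B" (Option B+). It gives no start date and no minimum duration, and does not refer to the period when baseline women were pregnant. The same section allocates 30 communities by simple randomisation, without strata.

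The baseline cohort in section 7.1 is retrospective: "this corresponds to infants born between April 1 and September 30, 2014". For endline the text gives births "corresponding to infants born between February 1 and July 31, 2015". Section 7.1 also states that "on average, women in Tanzania are 5.4 months pregnant at their first ANC visit when they have the initial opportunity to initiate ART".

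On the policy itself, section 2 says "In September 2013, Tanzania began rolling out 'Option B+' to all 6,270 reproductive and child health (RCH) facilities", and section 4 says that ANC, postnatal care and HIV care "are now provided in the majority of Tanzania's 6,270 reproductive and child health (RCH) clinics". Neither section gives a completion date or facility-level dates.

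Under Evaluation Question #1 (section 7.4) the analysis is fixed: "We will analyze all three measures through difference in difference strategy". The measures are timing of ART initiation, retention at 90 days postpartum, and adherence.

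**The concern.** Section 2 describes Option B+ as lifelong ART irrespective of clinical stage, with fewer steps before treatment. Whether a facility had switched when a woman first attended therefore bears on when she could start ART. A facility that switched during 2014 meets the rule in section 6.5, although some or all of its baseline women reached the usual first visit under the previous policy. Its endline women attend under Option B+. In such a facility the change from baseline to endline contains the policy switch as well as any intervention effect; in a facility that switched in 2013 it need not.

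Difference-in-differences removes a policy change that is shared equally by the arms. It does not remove one that happens to fall on more facilities in one arm than in the other. With 15 communities per arm and no stratification, such unevenness is quite possible. At stake is precision: a wider sampling distribution for the estimate, and lower power to detect the planned 13-point gain in retention.

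**Working it through.** **The plan's own figure.** Section 6.4 assumes 67% against 80% retention, ICC 0.05, 15 communities per arm and 80% power. Alpha is not stated; I take 0.05 two-sided. Two proportions with continuity correction need n = 195 per arm. With design effect 1 + (m − 1) × 0.05, m = 195 × 0.95 / (15 − 195 × 0.05) = 185.25 / 5.25 = 35.3, so 36 per community, and 15 × 35.3 = 529 per arm. The protocol gives 36 and 537, so the figure reproduces closely. The present point does not change it.

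**Dates.** Inputs: birth windows and mean first visit at 5.4 months (section 7.1). Assumptions: a 280-day pregnancy, 30.44 days per month, and births spread evenly.
- Time from first visit to birth = 280 − 5.4 × 30.44 = 115.6, about 116 days.
- Baseline LMP: about 25 June 2013 to 24 December 2013. The earliest baseline pregnancies began before roll-out.
- Baseline first visit: about 6 December 2013 to 6 June 2014, roughly 3 to 9 months into roll-out.
- Endline first visit: about 8 October 2014 to 6 April 2015.

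Share of each cohort reaching the mean first-visit point before the facility's start date (183 baseline birth dates):

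| Facility start | Baseline | Endline |
|---|---|---|
| 1 Oct 2013 | 0% | 0% |
| 1 Jan 2014 | 26/183 = 14% | 0% |
| 1 Feb 2014 | 57/183 = 31% | 0% |
| 1 Apr 2014 | 116/183 = 63% | 0% |
| 1 Jul 2014 | 183/183 = 100% | 0% |

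**Imbalance between arms.** Let L of the 30 facilities be late (assumption) and q = L/30. With 15 per arm, the between-arm difference in the late share has mean 0 and SD = √[q(1 − q) × (30/29) × (2/15)].
- L = 3: SD 0.111; chance of a difference of 20 points or more, about 22%.
- L = 6: SD 0.149; about 17%.
- L = 10: SD 0.175; about 25%.

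The chances do not rise steadily because the counts are discrete.

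**Carry-over to retention.** Let D be the absolute baseline gap in retention between late and other facilities, in percentage points (assumption). The SD added to the estimate is the SD above × D:

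| L | D = 10 | D = 20 | D = 30 |
|---|---|---|---|
| 0 | 0 | 0 | 0 |
| 3 | 1.11 | 2.23 | 3.34 |
| 6 | 1.49 | 2.97 | 4.46 |
| 10 | 1.75 | 3.50 | 5.25 |

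**Effect on power.** With 36 women per community and period and an assumed cluster autocorrelation of 0.8, the SE of the difference-in-differences is 4.48 points, and power for 13 points is about 83%.
- L = 3, D = 10: SE = √(4.48² + 1.11²) = 4.62; power about 80%.
- L = 6, D = 20: SE = √(4.48² + 2.97²) = 5.38; power about 68%.
- L = 10, D = 30: SE = √(4.48² + 5.25²) = 6.90; power about 47%.

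The starting power depends strongly on the autocorrelation: about 69% at 0.5 and 93% at 1.0, before any late facilities.

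**The case against.** A reader might infer that late-starting facilities bias the estimate. The documents do not support this. A facility's start date is fixed before allocation, so its expected imbalance is zero, and a start date common to all facilities cancels between arms. That objection stands in full.

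Nor do the documents show that any eligible facility started late. Sections 2 and 4 describe the country, whereas all communities come from one district council. Section 6.4 and its reference, an unpublished 2014 analysis of Option B+ patients in Shinyanga, show that the policy was running in the region by 2014. They do not show in which facilities. So L = 0 is possible, and the effect may be nil.

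It is also tempting to say that all three outcomes suffer equally. They do not. In a facility starting on 1 April 2014, every baseline birth falls on or after the start date. The window from 60 to 90 days postpartum runs from about 31 May to 29 December 2014, so a woman who booked earlier could still have started ART there. Adherence counts only days on which ART was prescribed (section 6.2), so a late start does not mechanically lower it.

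For retention even the direction is open. Section 6.2 defines it for women on ART. Section 3 reports that Option B+ patients starting in pregnancy were five times more likely never to return than women who started because they were eligible for treatment. On that definition, baseline retention in late facilities could be higher. Table 1 uses all HIV-infected pregnant women as the denominator, which could push it lower.

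A facility-wide gap is also a strong assumption. If a 20-point gap applies only to women booked before the switch, then with L = 10 the SD is 0.175 × 20 × 0.31 = 1.1 points for a February 2014 start and 0.175 × 20 × 0.63 = 2.2 points for an April start.

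Finally, adjustment for start date could sit in an SAP that is not shown. Eligibility and the randomisation scheme, however, are fixed in the protocol and cannot be repaired after allocation.

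**Conclusion.** The gap is real but limited. The rule in section 6.5 admits facilities that began Option B+ too late for some or all of their baseline women, and simple randomisation does nothing to even them out. The consequence is avoidable noise and chance imbalance, with no systematic bias in expectation. It bears most directly on timing of ART initiation and possibly on retention, in a direction that cannot be determined from the text. An effect on adherence is not established.

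The added SD on retention is zero with no late facilities, about 1 point with 3 late facilities and a 10-point gap, and about 5 points with 10 late facilities and a 30-point gap, against the 13-point target. Both the number of late facilities and the gap are assumptions. The dates and shares rest on the protocol's mean booking time applied to every woman; real booking times vary, so some women fall either side of these limits. The limitations section names time as a possible confounder, but measuring at 90 days postpartum does not deal with a policy change at the facility between the two cohorts.

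**What to change.** In section 6.5, add one sentence: the linked RCH facility must already have been providing Option B+ before the baseline cohort's first ANC visits, that is, by about 1 December 2013 or earlier. The date comes from a mean, so an earlier one would cover more of the early bookers. Check facility start dates before selection.

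If too few facilities qualify, record each facility's start date before allocation, and stratify the randomisation by it or adjust for it.

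Do not restrict the baseline cohort to women whose first ANC visit came after the facility's start date. Among the earlier births this keeps the late bookers, which would raise baseline gestational age at ART start in those facilities only. It would also drop women with no ANC visit, whom section 7.2 is at pains to capture through the CHW logs.

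The cost is a look-up of start dates and a somewhat smaller pool of eligible communities. No new procedures or data collection from women are needed.

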### 6.4 Sample Size and Power

In health facilities where there are  $< 50$  HIV-infected pregnant or postpartum women in the baseline or endline cohorts (determined with the ANC register), we will abstract data from the ART register on all women. At health facilities where there are  $\geq 50$  HIV-infected pregnant or postpartum women in the cohorts, we will abstract a predetermined sampling fraction such that 75% of women are sampled from cohorts with 50-100 women, 50% of women are sampled from cohorts with 100-200 women, etc. This approach will ensure that the sample size is adequate to detect a minimum increase in retention in care at 90 days postpartum.

We have powered the study for the outcome of retention in care 90 days postpartum. In our aforementioned preliminary analysis of pregnant women in Shinyanga, we found that more than

36% of HIV-infected pregnant women who initiated ART were lost within 100 days. Thus, we will conservatively assume that in the comparison communities, 67% of women will be retained in care at 90 days postpartum. For logistical and budgetary reasons, especially given the rapid nature of the impact evaluation, we have determined that we can reasonably study 15 intervention communities (a total of 30 CHW, 2 per village, and 15 RCH facilities) and 15 comparison communities.

If we assume an ICC of 0.05 and that the intervention will increase the proportion of women who are retained in care 90 days postpartum from 67% to 80% (detectable effect size of 13 percentage points, or 20%), we will require at least 36 observations per community, or 537 observations from the intervention and comparison groups, to have 80% power to reject the null hypothesis of no effect. Obtaining data from at least 36 HIV-infected women per facility is well within the normal volume of clients at RCH clinics, as many RCH clinics initiate an average of 11 HIV-infected women on ART/ARVs per month. With at least 6 intervention months in each community, we will ensure that we can easily meet this goal.

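### Simple randomisation of 30 communities leaves imbalance in facility volume and underlying retention to a difference-in-differences analysis that the sample size does not reflect; stratified or constrained allocation would be a cheap gain in precision and credibility

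*Protocol*

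**What the plan says.** Section 6.5 states the pool, "We will identify 30 similarly sized communities in Shinyanga District Council", and allocates it "using simple randomization (using the sample command in STATA"). No stratification, matching or constraint is named. Section 6.4 fixes the split: "15 intervention communities (a total of 30 CHW, 2 per village, and 15 RCH facilities) and 15 comparison communities".

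Before allocation, section 6.5 restricts entry to communities in one district council that have an active cadre of community health workers, "have similar numbers of households and schools", are noncontiguous or naturally separated, and lie within 5 km of a facility providing Option B+. HIV caseload at the facility and past retention are not among the criteria.

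On the outcome, section 6.4 says "We have powered the study for the outcome of retention in care 90 days postpartum" and assumes that in comparison communities "67% of women will be retained in care at 90 days postpartum", rising to 80% with the intervention, at an ICC of 0.05. Sections 6.3 and 7.1 plan a baseline and an endline cohort, and section 7.4 analyses all three impact outcomes by difference-in-differences. Section 7.2 lists the ANC and ART registers as data sources.

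**The concern.** With 15 clusters per arm, simple randomisation can leave the arms noticeably different in cluster-level predictors of the outcome. Communities with similar numbers of households and schools can still differ in HIV caseload and in how well their facility keeps women in care. The assumed ICC of 0.05 itself presumes that retention varies between communities that meet the eligibility rules.

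The protocol relies on the difference-in-differences analysis to deal with this. That analysis does subtract a baseline arm difference in retention. However, it subtracts a noisy quantity, it does not remove time trends that differ by facility volume, and the sample size was not calculated for it. At stake are the precision of the 13-point contrast and how easily a 30-cluster result could be disputed because the arms looked different at baseline.

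**Working it through.** **Inputs** (section 6.4): 67% versus 80%, ICC 0.05, 15 communities per arm, 36 women per community, 80% power. Alpha is not stated; 0.05 two-sided is assumed because it reproduces the stated number.

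**1. The plan's own figure.** The two-proportion formula with continuity correction gives 195 per arm. Design effect: 1 + (36 − 1) × 0.05 = 2.75. Then 195 × 2.75 = 536.25, rounded up to 537 per arm, and 536.25 / 15 = 35.75, so 36 per community. The figure reproduces as an endline-only comparison. No baseline term enters.

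**2. Chance imbalance in true underlying retention.**
- Between-community SD = √(0.05 × 0.67 × 0.33) = 0.105, or 10.5 points.
- SD of the arm difference = 10.5 × √(2/15) = 3.8 points; 95% range ±1.96 × 3.84 = ±7.5 points.
- Chance of more than 5 points (normal approximation): 19%. More than 6.5 points, half the target effect: 9%.
- By ICC, chance of more than 5 points: 0.4% at 0.01, 4% at 0.02, 19% at 0.05, 36% at 0.10.

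**3. Where this variance sits.** With 67% in both arms, the full standard error at 36 per community is √(2 × 0.67 × 0.33 × 2.75 / 540) = 4.7 points. It splits into the 3.8-point between-community part and a within-community part of √(2/15 × 0.95 × 0.2211 / 36) = 2.8 points (3.8² + 2.8² ≈ 4.7²). The chance imbalance is thus part of the planned standard error.

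**4. What differencing costs.** Let c be the correlation over time of community-level retention; the protocol does not give it. The correlation between a community's observed baseline and endline rates is r = c × 0.05 / (0.05 + 0.95/36) = 0.65c. The variance of the difference-in-differences is 2(1 − r) times that of the endline contrast. The endline standard error, using the mean of 0.67 × 0.33 and 0.80 × 0.20 (0.1906) for both periods, is √(2 × 0.1906 × 2.75 / 540) = 4.4 points.

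| Assumed c | Power, difference-in-differences | Power, baseline-adjusted | Power, endline only |
|---|---|---|---|
| 0 | 55% | 84% | 84% |
| 0.2 | 61% | 85% | 84% |
| 0.5 | 72% | 88% | 84% |
| 0.8 | 86% | 93% | 84% |
| 1 | 94% | 97% | 84% |

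Differencing loses power when r < 0.5, that is, when c is below about 0.5 / 0.6545 = 0.76.

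**5. What stratification could buy.** In 20,000 simulated allocations with five strata of six communities, allocated 3:3 within each, the results depend on the correlation between the stratifier and true retention. The correlations are assumptions.

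| Assumed correlation | SD of true imbalance | Chance above 5 points | Full standard error |
|---|---|---|---|
| none (simple) | 3.8 | 19% | 4.7 |
| 0.5 | 3.4 | 14% | 4.4 |
| 0.7 | 2.9 | 8% | 4.0 |
| 0.8 | 2.5 | 5% | 3.8 |

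The last column is √(SD² + 2.8²), from unrounded values.

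**6. Which correlations are plausible.** If earlier retention from 36 women is the stratifier, its reliability is 0.05 / (0.05 + 0.95/36) = 0.65, so its correlation with true retention in the same period is at most √0.65 = 0.81. With c of 0.5 or 0.8, it falls to 0.81 × 0.5 = 0.40 or 0.81 × 0.8 = 0.65. The upper rows of the table in step 5 are therefore the more realistic.

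**7. What is known at allocation.** Section 7.1 says that women giving birth from 1 February 2015 had at least the last four months of pregnancy exposed, which implies a start around October 2014. The baseline cohort reaches 90 days postpartum up to 31 December 2014, so it is incomplete at allocation.

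**The case against.** The case for leaving the plan alone has real force.

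- A reader might infer that imbalance is left wholly uncontrolled. It is not: the baseline cohort and the difference-in-differences analysis remove a baseline arm difference in retention, and eligibility limits differences in community size.
- A reader might infer that simple randomisation biases the result, or that the 19% is an extra risk on top of the plan. Neither follows. Randomisation keeps the test valid, and step 3 shows that the 3.8 points are already paid for through the design effect.
- A reader might take the abstraction rule, for example "50% of women are sampled from cohorts with 100-200 women", as evidence that the 30 facilities span a several-fold range of volume. It is a contingency rule for whatever cohort sizes occur, not a forecast, and nowhere does the protocol say that volume predicts retention.
- Past retention is not a simple count. It needs matching between ANC and ART registers, partly on paper, and the planned baseline cohort is not complete in time.
- Baseline adjustment in place of differencing would recover precision under simple randomisation, as step 4 shows, and an analysis plan that is not at hand may provide for it.

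All of this stands. It reduces the point to precision and credibility and makes the gain uncertain. It does not give a reason to prefer unrestricted allocation when facility cohort size can be counted from registers that the trial will use anyway. Restriction also has to be decided before allocation, whatever the analysis plan says.

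**Conclusion.** The point holds as a low-cost improvement, not as an error that invalidates the design. Facility HIV volume and underlying retention are not balanced at allocation, and the analysis left to handle this is not the one for which the sample size was calculated. On the plan's inputs, the true arm imbalance has an SD of 3.8 points and a 19% chance of exceeding 5 points. This falls to 4% if the ICC is 0.02. The benefit of restricting allocation rests on how well the stratifiers predict retention, which the protocol does not give. At an assumed correlation of 0.5 the full standard error falls only from 4.7 to 4.4 points. Larger gains need correlations that a noisy register measure is unlikely to reach.

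**What to change.** In section 6.5, replace simple randomisation with stratified or constrained 15:15 randomisation. Count HIV-infected pregnant and postpartum women per RCH facility in the ANC registers for a period before allocation, rank the 30 communities on that count, form five strata of six, and allocate 3:3 within each using seeded Stata code. Add earlier register retention as a second factor only where it is readily available, taken from before the intervention starts because the planned baseline cohort will not be complete. Section 2 dates the Option B+ roll-out from September 2013, so earlier records should exist.

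Include the strata in the analysis, and state in section 6.4 how the sample size relates to the difference-in-differences analysis.

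The cost is one set of register counts before allocation, a few lines of code, and a few degrees of freedom (four for five strata, out of 28 for a comparison of 30 community means). Adding past retention costs more, because it needs linked register abstraction.
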